#### Recruitment {15}

Patients from 10 hospital outpatient clinics and inpatients admitted in the department of nephrology will be recruited. The study doctor is responsible for the screening process. The study doctor identifies the potential participants and asks them to participate in the study. Patients will be given sufficient time to consider their participation in the research. Before they decide to participate in this study, discussion with their family and friends is encouraged. If the potential participants have questions regarding the trial, they can ask the research doctor/researcher and will be provided with sufficient explanation until their full understanding is confirmed. To ensure smooth enrollment and shorten enrollment time, all research centers will adopt an effective enrollment strategy to ensure that sufficient study participants are included. We will use the WeChat app (a popular social communication app in China), hospital posters, and oral introduction by the doctor for promotion.

### Methods: assignment of interventions

#### Sequence generation {16a}

Central randomization will be used as a randomization method, and the random number will be generated and assigned by the designated data management center. We will use simple randomization for random allocations. Eligible patients will be randomly assigned to the aspirin group or the placebo group. The treatment will last for 36 months.

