The relationship between CKD platelet activation and accelerated atherosclerosis has drawn considerable attention in recent years. Other researchers and our previous studies have found that abnormal platelet activation is manifested by an increase in platelet reactivity in CKD patients and animal models [13–15]. Previous extensive population-based studies have shown that atherosclerosis is highly prevalent in CKD patients, thus increasing the risk of cardiovascular and all-cause mortality. CKD patients have more severe atherosclerosis than age- and sex-matched controls from the general population [6]. The NEFRONA study has indicated that the incidence rates of carotid atherosclerosis are 50.8% in patients with CKD and 69% in diabetic patients with CKD [16]. Currently, antiplatelet drugs are widely used to prevent CVD, especially intravascular thrombosis. Antiplatelet drugs can reduce CVD deaths by 15% and CVD incidence by 20% in high-risk patients [17]. The American Heart Association recommended that antiplatelet drugs can be used as a secondary prevention strategy for patients with high blood pressure, muscular atrophy, obesity, diabetes, or a family history of ischemic heart disease [17]. Although antiplatelet drugs have been shown to reduce the risk of CVD in patients with CKD, the benefits and evidence of using antiplatelet agents in CKD patients remain unknown. A previous meta-analysis showed that antiplatelet drugs could reduce the risk of myocardial infarction in patients with CKD but were not associated with all-cause and cardiovascular mortality [18]. Simultaneously, the SWEDEHEART study demonstrated that dual antiplatelet therapy could reduce the risk of all-cause mortality, stroke, and reinfarction in acute coronary syndrome patients with CKD [19]. Aspirin is widely used and recommended as the first-line antiplatelet drug in the clinical setting. However, a previous meta-analysis indicated that aspirin had no apparent benefits on the primary prevention of CVD in the CKD population [20]. Thus, the efficacy and safety of antiplatelet therapy, like aspirin, in patients with CKD remain controversial. The evidence is not considered robust as previous researches were small sample cohort studies and lacked large clinical randomized controlled (RCT) studies. In addition, CKD patients were excluded or only those with mild CKD (CKD stages 1–2) were recruited in previous extensive RCT studies to assess the efficacy of antiplatelet therapy. Thus, the use of antiplatelet therapy in patients with CKD has fundamental clinical significance. Therefore, a prospective RCT trial must be performed to determine the significance of antiplatelet therapy in CKD patients.

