### Sample size {14}

#### Sample size estimation

The sample was calculated as follows: $$ n=\frac{{\left({z}_{\alpha}\sqrt{2\overline{pq}}+{z}_{\beta}\sqrt{p1q1+p0q0}\right)}^2}{{\left(p1-p0\right)}^2} $$

In this study, p0 and p1 represent the estimated exposure rates of the control group and the experimental group, respectively, while *Z*_α_ and *Z*_β_ indicate the standard positive distribution boundaries. In the table, when *α* or *β* is equal to 0.05, its value is 1.96; when *α* or *β* is equal to 0.01, its value is 2.58. In this study, the incidence of p0 is above 40% [8]. After the intervention, p1 is expected to decrease by 15% compared with p0 (p1 = 25%). Let *α* = 0.05 (both sides), and *β* = 0.10. The calculated minimum sample size is 251; if 10% of the cases were lost to follow-up, the calculated sample size would be 277 for each group, and approximately 554 patients will be included in the trial.

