#### Concealment mechanism {16b}

To assure concealment, we will use an online central randomization service to randomize the participants. When baseline measurements and the confirmation of eligibility are completed, then the sequence will be revealed.

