### Statistical analysis

#### Statistical methods for primary and secondary outcomes {20a}

For the primary outcome, the chi-square test will be performed to compare the occurrence rate of atherosclerosis at 1, 2, and 3 years of follow-up between the aspirin group and the placebo group. For the secondary outcome, the chi-square test will be performed to compare the combined cardiovascular events and all-cause mortality at 1, 2, and 3 years of follow-up between the aspirin group and the placebo group. Then, the decrease in eGFR will be computed using the value measured at the last follow-up minus the value measured at baseline; patients with a 50% decline in eGFR will be treated as patients who experienced an eGFR reduction of 50%. Similarly, the proportion of patients with an eGFR reduction of 50% between the aspirin group and the placebo group will be compared using the chi-square test. If the previous comparison did not reach a significant difference, the magnitude of decrease in eGFR between the two groups would be compared using two independent sample *t* tests or the Mann-Whitney *U* tests. In addition, multivariate competing-risk regression models will be used to assess the independent effect of treatments adjusted for age, sex, diabetes, serum lipid profiles, and phosphorus.

All statistical analyses will be performed using the SPSS software version 21.0 (IBM Corp., Armonk, NY, USA), and general data will be expressed as mean ± standard deviation. The variables with normal distribution and variance will be compared. One-way analysis of variance will be used for comparisons within groups. The SNK test will be used for multiple comparisons between groups. Pearson’s correlation analysis will be used for analyzing the correlation between variables. A nonparametric test will be used to analyze variables that do not meet the parameter test conditions. The Kruskal-Wallis *H* test or Mann-Whitney *U* test will be used for data comparison. Spearman’s correlation analysis will be used for correlation analysis. The chi-square test will be used for comparison. A *p* value of < 0.05 will be considered significant. A nonparametric test for multiple comparisons will be corrected using the Bonferroni method, *p* < 0.008, statistically significant safety analysis.

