## Discussion

Previous epidemic studies reported that the incidence rates of atherosclerosis in non-diabetic and diabetic CKD patients are 50% and 69%, respectively [16, 22]. The incidence of atherosclerosis in non-diabetic CKD patients was also proven by conducting an imaging analysis in a Korean study, which enrolled more than 3000 individuals without known CAD who underwent coronary computed tomography angiography. This study showed that 34.1% and 48.6% of the individuals with mild (eGFR 60–89 mL/min/1.73 m^2^) and moderate (eGFR 30–59 mL/min/1.73 m^2^) CKD had segment vessel stenosis and stenosis of ≥ 50%, respectively [23]. Aspirin has been shown to improve atherosclerosis in animal models. Aspirin-triggered lipoxins A4 (ATL4) is an effective anti-inflammatory mediator involved in inflammation regression. ATL4 reduced the macrophage infiltration and apoptosis in ApoE−/− mice with atherosclerosis in the aortic roots and thoracic aorta [24]. This indicates that aspirin can inhibit the expression of nuclear factor-kappa B1 and deactivate the cAMP signaling pathway to treat atherosclerosis [25]. Inflammation plays a vital role in the pathophysiology of atherosclerosis, and aspirin has significant anti-inflammatory properties. In Chai et al.’s study, orchidectomized Sprague-Dawley rats fed with a AIN-93 M casein-based control diet for 4 months developed atherosclerotic lesions. After treatment with aspirin (500 mg/kg) for 3 months, the fatty streak area was completely reversed, and the atherosclerotic lesions disappeared [26]. Therefore, the theoretical mechanism and arterial test of aspirin support its role in improving atherosclerosis.

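### Simple randomisation with an unadjusted chi-square is valid, but leaves centre unhandled throughout and diabetes out of the allocation and primary test; stratifying and adjusting is a cheap, optional gain

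*Protocol article*

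**What the plan says.** **Allocation.** Sequence generation {16a}: "We will use simple randomization for random allocations". No stratification factor, block or minimisation factor is named. Concealment mechanism {16b} adds that "we will use an online central randomization service to randomize the participants", once baseline measurements and the eligibility check are complete.

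**Centres.** Recruitment {15}: "Patients from 10 hospital outpatient clinics and inpatients admitted in the department of nephrology will be recruited".

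**Primary test.** Statistical methods {20a}: "For the primary outcome, the chi-square test will be performed to compare the occurrence rate of atherosclerosis". No covariate is attached to this test.

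**Adjusted model.** The same section then says that "multivariate competing-risk regression models will be used to assess the independent effect of treatments adjusted for age, sex, diabetes, serum lipid profiles, and phosphorus". Centre is not in the list, and the sentence does not say which outcome is modelled.

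**Diabetes as a predictor.** Discussion: "the incidence rates of atherosclerosis in non-diabetic and diabetic CKD patients are 50% and 69%, respectively". Background {6a} gives "50.8% in patients with CKD and 69% in diabetic patients with CKD"; there the comparator is CKD patients in general, not non-diabetic patients.

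**Reading of the outcome.** The Outcomes section says that an experienced sonographer performs the carotid ultrasound on one named device model. It does not say where, or by how many readers, images are read, and it describes no central reading.

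**The concern.** Two baseline factors could plausibly move the primary outcome. The sponsor itself treats diabetes as prognostic, by citing the gap and by adjusting for diabetes in a later model. Centre could matter because plaque is called against sub-millimetre and percentage thresholds, and nothing described removes reading differences between sites. Such differences are possible; the protocol does not show that they exist.

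Simple randomisation balances neither factor except on average, and the primary test corrects for neither. What is at stake is precision, and how convincing the primary contrast looks if a visible imbalance occurs. The protocol already has what is needed to do better: a central online system, randomisation after baseline assessment, comorbidities recorded as basic information, and a stated pre-recruitment status.

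**Working it through.** **Inputs from the protocol.** N = 554 (277 per group); 10 centres; control rate 0.40 and aspirin rate 0.25, a 15-point difference; two-sided alpha 0.05; diabetes gap of 19 points (69 − 50, Discussion) or 18.2 points (69 − 50.8, Background).

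**Assumptions, because the protocol gives no figure.** Diabetic share 20–50%; equal centres of about 55; between-centre SD of the outcome on the logit scale 0, 0.3 or 0.6; the cited gap applies to new disease over 36 months in this population.

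**1. The plan's sample size.** The printed formula gives (1.96·√(2·0.325·0.675) + 1.645·√(0.24 + 0.1875))² / 0.15² = 250.4, so 251, and 251 × 1.10 ≈ 277. The stated figures reproduce with 1.645 as the beta quantile. Power is then about 95% at 251 per group and 96.7% at 277, which leaves little room for a gain at the planned effect.

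**2. Arm size.** Binomial(554, 0.5): the 95% range for one arm is 254 to 300. At that extreme the efficiency relative to equal arms is 4·254·300/554² = 0.993, a negligible loss.

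**3. Diabetes imbalance.** The SE of the between-arm difference in diabetic share is √(4·d(1−d)/554), where d is the diabetic share. The shift in the risk difference is imbalance × gap.

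| Diabetic share (assumed) | SE (points) | 95% limit (points) | P(difference > 5 points) | Shift at the limit (19-point gap) |
|---|---|---|---|---|
| 20% | 3.4 | 6.7 | 14% | 1.3 |
| 30% | 3.9 | 7.6 | 20% | 1.5 |
| 40% | 4.2 | 8.2 | 23% | 1.6 |
| 50% | 4.2 | 8.3 | 24% | 1.6 |

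With the 18.2-point gap the ends are 6.7 × 0.182 = 1.2 and 8.3 × 0.182 = 1.5, so the range is about 1.2–1.6 points. The SE of the risk difference is √((0.24 + 0.1875)/277) = 3.9 points, so even this tail shift is about 0.4 SE.

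**4. Centre imbalance.** Binomial(55, 0.5): a split of 35:20 or worse has probability 5.8% per centre, so 1 − (1 − 0.058)¹⁰ = 45% for at least one of ten. For scale, let one centre split 35:20 and the other 499 patients split evenly. That centre then supplies 35/284.5 = 12.3% of one arm and 20/269.5 = 7.4% of the other. For every 10 points by which its event rate departs from the rest, the contrast moves by about 0.049 × 10 = 0.5 points.

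**5. What the change buys.** Simulation with 5,000 replicates per cell, all 554 analysed, 40% diabetic, 19-point gap. Simple allocation with chi-square is compared with blocks of 4 within centre and diabetes plus a Cochran-Mantel-Haenszel (CMH) test.

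| Centre SD (logit) | Type I error: simple / stratified | Power, 40% vs 25% | Power, risk ratio 0.75 |
|---|---|---|---|
| 0 | 5.2% / 5.0% | 96.8% / 97.4% | 69.6% / 69.9% |
| 0.3 | 4.4% / 5.5% | 96.4% / 97.1% | 69.5% / 71.5% |
| 0.6 | 5.0% / 4.9% | 96.5% / 97.0% | 70.2% / 74.1% |

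The Monte Carlo SE of one power figure is about 0.2 points near 97% and 0.6 points near 70%, so the differences in the middle column are barely distinguishable from noise. At SD 0.6 and risk ratio 0.75, keeping simple allocation but using CMH gave 72.5%, so more than half of the 4-point gain comes from the adjusted analysis alone. Stratified allocation analysed with the unadjusted chi-square had a type I error of 3.9% at SD 0.6. That is why the factors should be carried into the analysis.

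**The case against.** The strongest reply is that nothing here is an error. Simple randomisation at N = 554 with a chi-square test is a valid design. Chance imbalance is already part of the test's sampling variance, so it is not an uncorrected bias. Simple randomisation is also the least predictable scheme. All of this stands, and it limits the point to efficiency and robustness.

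Three stronger readings are tempting, and the protocol does not support them:

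- *A reader might infer that diabetes is left uncontrolled altogether.* It is not: the competing-risk model adjusts for it. The gap is confined to the allocation and the primary test.
- *A reader might infer that each hospital reads its own scans.* The text only refers to an experienced sonographer. No central reading is described, but local reading is not stated, and no between-site difference in reading or outcome is given. The 45% figure shows uneven splits, not a distorted result.
- *A reader might take the 18–19-point gap as the effect of diabetes in this trial.* It comes from other CKD cohorts. This trial enrols patients without carotid atherosclerosis at entry and plans on a control rate of about 40%, so the gap for new disease over 36 months could differ.

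What survives is that centre is absent everywhere, and that a factor the sponsor regards as prognostic is missing from the primary comparison.

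**Conclusion.** The point holds as a modest improvement, not as a flaw in validity. Centre is the stronger half, because uneven splits at some sites are likely and no allocation or analysis step deals with site. Diabetes is the weaker half, because a supplementary model already covers it.

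Under the assumptions above, a tail-case diabetes imbalance moves the contrast by well under one standard error. The expected power gain is below 1 point at the planned effect. It reaches about 4 points only if the effect is weaker than planned and centres differ a great deal. The required sample size does not change.

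**What to change.** Before first enrolment, as an optional change:

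1. In the existing central online system, stratify by centre and diabetes using permuted blocks of concealed, varying size, or minimise on the same factors with a random element. Ten centres by two diabetes groups gives 20 strata, averaging 554/20 ≈ 28 patients.
2. Make the primary 36-month comparison a Mantel-Haenszel risk difference, or a logistic model, adjusted for centre and diabetes. Keep the unadjusted chi-square as a sensitivity analysis.

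Make the two changes together. If enrolment has already begun, the second is still worthwhile provided it is fixed before unblinding.

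The cost is a setting in the randomisation system, a short change of text, and slightly greater predictability of allocation within centre. Varying block sizes limit that predictability, and it matters little if the trial is double-blind as the Blinding section says. The Trial design section calls the study open, so the two sections should be reconciled when this cost is weighed.

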#### Concealment mechanism {16b}

To assure concealment, we will use an online central randomization service to randomize the participants. When baseline measurements and the confirmation of eligibility are completed, then the sequence will be revealed.

#### Implementation {16c}

First, the research doctor will complete the baseline measurements and assess if the participants conformed to all the inclusion/exclusion criteria. Finally, the research doctor will use the online central randomization service to assign the participant and complete the assessments and the randomization.

### Assignment of interventions: blinding

#### Who will be blinded {17a}

The study is a double-blind study. The included patients will not be informed about the group to which they belong. The investigators in each center will not know which patients receive active drug or inactive drug.

#### Procedure for unblinding if needed {17b}

If no pregnancy or other emergency occurs during the research period, the blinded participants will be unblinded according to the standard procedure when serious adverse events occurs. If the drugs used in the study have an impact on the treatment, emergency unblinding will be considered.

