**Methods/design:**

The ALTAS-CKD study is a multicenter, prospective, randomized, double-blind, placebo-controlled trial of 554 adult patients with stage 3–5 non-dialysis-dependent CKD recruited from 10 territory medical centers in China. A secured web-based computer randomization system will be used to administer aspirin 100 mg once daily or a matching inactive placebo for 36 months. The primary endpoint will be the occurrence of atherosclerosis, as measured by carotid ultrasonography. The secondary endpoints will be combined cardiovascular events, all-cause mortality, and 50% decrease in the estimated glomerular filtration rate.

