### Trial design {8}

This study is a prospective, open, randomized, controlled multicenter study initiated by the Second Affiliated Hospital of the Army Medical University (Xinqiao Hospital) and approved by the ethics committee of Xinqiao Hospital. An exploratory design will be to investigate the efficacy and safety of aspirin for preventing atherosclerosis in patients with CKD stages 3–5. All eligible patients will be randomly assigned to either the aspirin group or the placebo group (Fig. 1).

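### The trial is labelled both open and double-blind, and its unblinding rule makes a serious adverse event in itself a trigger, so unblinding would depend on outcome

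*Protocol article*

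**What the plan says.** On the design label, the protocol article makes two incompatible statements.

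- Trial design {8}: "This study is a prospective, open, randomized, controlled multicenter study".
- Abstract, Methods/design: "multicenter, prospective, randomized, double-blind, placebo-controlled trial". Who will be blinded {17a}: "The study is a double-blind study".

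Section {17a} goes on to say who is masked: "The included patients will not be informed about the group to which they belong", and "The investigators in each center will not know which patients receive active drug or inactive drug". The abstract and Intervention description {11a} both describe a placebo made to match aspirin.

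On breaking the blind, Procedure for unblinding if needed {17b} has two sentences. The first opens with a condition about the absence of pregnancy or another emergency and then states that "the blinded participants will be unblinded according to the standard procedure when serious adverse events occurs". The second says that emergency unblinding will be considered where the study drug bears on treatment.

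On outcomes, Outcomes {12} has an experienced sonographer read carotid plaque at 6, 12, 24 and 36 months, with month 36 as the primary time point. Secondary outcomes lists infarction, heart failure leading to hospital admission and severe arrhythmias including cardiac arrest, recorded at every visit over three years.

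**The concern.** Two things need attention, and they differ in weight.

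The label is a plain contradiction about a core design feature, and it sits in the section that defines the design.

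The unblinding rule matters more. It is worded as what will happen, and its trigger is the serious adverse event itself. Whether anyone needs to know the allocation enters only in the next sentence, as a separate and weaker route. Several secondary endpoints would normally qualify as serious adverse events, so having an endpoint could itself reveal the arm. Follow-up then continues with events still to be classified and scans still to be read. Plaque is called at cut-offs of 0.5 mm, 50% of the surrounding intima-media thickness, or 1.5 mm, which leaves room for operator judgement. Classifying some cardiovascular events, such as other acute coronary syndromes, also involves judgement. If the people making those calls know the arm, the comparison can shift in either direction, and the double-blind claim is weakened for the patients who have had events.

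**Working it through.** The plan gives no figure on this point, so there is none to reproduce. The check is a comparison of the text, followed by two illustrations on assumed inputs.

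**1. Which label fits.** Section {8} says open but itself assigns patients to an aspirin or a placebo group. The abstract, {11a} and {17a} all describe masking: a matching tablet, uninformed patients and centre investigators unaware of treatment. Nothing describes open-label conduct. Double-blind fits the rest of the text.

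**2. What {17b} does as written.** The opening condition is garbled: taken literally, unblinding for a serious adverse event applies when there is no emergency. On any reading, the trigger in the first sentence is the event, with no condition that the allocation be needed. The section does not say who is told.

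**3. What could be exposed.**

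- The triggering event has already happened, so only its classification is open to influence.
- Later events and later scans are open to influence, including the month-36 scan for anyone unblinded before it.
- Patients without a serious adverse event stay masked, and scans read before any unblinding are unaffected.
- All-cause mortality leaves little room for judgement.

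**4. How many patients (assumed rates).** The documents give no serious-adverse-event rate. Assume a constant rate r of first events per patient-year over the 3 years. The share with at least one event is 1 − exp(−3r), applied to the planned 554:

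- r = 0.05: 1 − exp(−0.15) = 13.9%, about 77 patients
- r = 0.10: 1 − exp(−0.30) = 25.9%, about 144 patients
- r = 0.20: 1 − exp(−0.60) = 45.1%, about 250 patients

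At each assumed rate this is an upper bound on patients unblinded with a scan still to come, because it ignores deaths, dropout and events after the last scan.

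**5. What that could do to the primary test (assumed misreading).** The count in step 4 measures unblinding, not bias. For a sense of scale, take the plan's printed 251 per arm, no true effect and its 40% control rate in both arms. Let a share f of aspirin patients be unblinded, and let a share m of their positive scans be read as negative by a sonographer who knows the arm. The aspirin rate becomes p1 = 0.40 × (1 − f·m), and the apparent difference is d = 0.40 − p1. The two-sided rejection probability is

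1 − Φ((1.96·se0 − d)/se1) + Φ((−1.96·se0 − d)/se1),

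with se0 = √(2·p̄(1 − p̄)/251), se1 = √((0.40·0.60 + p1(1 − p1))/251) and p̄ the mean of the two rates.

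For f = 20% and m = 25%: p1 = 0.38, d = 0.02, and se0 and se1 are each about 0.0435. The two tails are about 6.67% and 0.78%, or 7.45% in total against a nominal 5%.

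| f | m = 10% | m = 25% |
|---|---|---|
| 10% | 5.10% | 5.60% |
| 20% | 5.38% | 7.45% |
| 30% | 5.87% | 10.61% |

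The inflation is small unless a sizeable share is unblinded and the misreading is marked and in one direction.

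**The case against.** The strongest reply is that both items are drafting faults in a trial that is plainly meant to be double-blind. On the label this is persuasive: a reader might infer from {8} that the trial is to be run open, but the placebo group in that same section and the masking in {17a} do not support that. The error should still be corrected.

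On {17b}, the reply is that the sentence is garbled, that its heading says if needed, that a standard procedure not shown may govern disclosure, and that nothing says the allocation reaches sonographers or event classifiers. The last point stands: exposure of the readers is possible, not stated. But an unseen procedure would govern how and to whom the code is released, whereas the trigger is fixed here. That makes it a badly worded rule, not a detail left to the full protocol.

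A reader might also infer a third fault from Concealment mechanism {16b}, where once eligibility is confirmed "then the sequence will be revealed", taken with Implementation {16c}, where the research doctor operates the service. That section concerns when an assignment is released, and {17a} says centre investigators will not know the treatment. It is not a separate error.

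Finally, it is tempting to say that nearly every patient with a non-fatal cardiovascular endpoint would be unblinded. The documents do not support this. The endpoint list includes primary atrial fibrillation or flutter and severe sinus bradycardia, which need not be serious, and the article does not define seriousness.

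**Conclusion.** The point holds in limited form. The open label contradicts the rest of the article and must be reconciled with it. The unblinding rule, followed as written, makes breaking the blind depend on events that overlap the secondary endpoints. It could therefore affect event classification, later events and later carotid scans up to month 36.

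The documents do not show that the primary outcome or the event counts are unprotected as a whole. Masking by matching placebo remains for every patient without a serious adverse event, and mortality is little affected.

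The size cannot be computed from the documents. The 14% to 45% range rests entirely on the assumed 0.05 to 0.20 first events per patient-year and is an upper bound at each rate. The type I error figures of 5.10% to 10.61% rest on further assumptions about misreading, and on the allocation reaching the sonographer. The case for changing the text rests on the wording of the rule, not on these numbers.

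**What to change.** 1. In Trial design {8}, correct the open label so that it agrees with the abstract and {17a}.
2. Reword {17b} so that a serious adverse event alone does not automatically break the blind. Remove the garbled opening condition and reconcile the two sentences, so that code-break is per patient and tied to need for the allocation. When that need arises is a clinical decision for the sponsor and investigators to define.
3. State that the allocation is not disclosed to sonographers or to those classifying events, including after a code-break.
4. Report the unblinded patients by arm.

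Trial status places the trial before recruitment, so the first three items are wording changes to the protocol and the fourth is one table in the report. No sample-size change or new assessment is needed. Made later, the change could not restore the blind for patients already unblinded.
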